
#### Other outcome measures

Montreal Cognitive Assessment (MoCA): the MoCA is a brief screening tool to detect mild cognitive impairment. It covers multiple cognitive domains, including short-term memory recall, visuospatial abilities, executive functions, attention, concentration, language and orientation.^58^ The test yields a total score out of 30, with a score of 26 or above generally considered normal. It is commonly used to screen for cognitive deficits in stroke and other neurological populations.Physical Activity Enjoyment Scale (PACES): the PACES assesses enjoyment related to physical activity through statements such as ‘I enjoy it’ or ‘It’s no fun at all’, rated on a Likert scale.^59^ Higher total scores indicate greater enjoyment of exercise. It is used to understand motivation and predict adherence to physical activity programmes.

### Intervention-related cost evaluation

All direct intervention costs related to implementing the RGM across the four sites will be systematically captured and reported. These costs will include trainer fees, facility usage, equipment and materials, staff time for coordination and administration.

### Focus group interviews

Focus group interviews will be conducted to shed light on how participants and RGM trainers subjectively experience RGM training. Through these focus group interviews, the aim is to explore participants’ experiences of engaging with the RGM in a social setting, identify factors that influence motivation, engagement and adherence to the exercise programme, and generate insights on how RGM training could be further tailored to meet the needs of individuals living with stroke. Additionally, the interviews will highlight the trainers’ perspectives on adapting the tempo, music selection and exercises for this specific target group. Focus groups with participants and RGM trainers will be conducted separately and in person to ensure that both perspectives are captured in depth. An interview guide developed to structure these sessions is provided in online supplemental file 3.

### Recruitment procedure

Recruitment will take place via advertisements in Gothenburg, Karlstad, Stockholm, Malmö and through outreach to local stroke associations, which has already been completed. The advertisement will be shared on relevant Facebook pages for stroke survivors, including Stroke Mitt I Livet (‘stroke in midlife’), a targeted initiative within stroke associations across Sweden for individuals who experienced stroke during working age. Interested individuals will be instructed to email the responsible researcher (PP) to register their interest. Follow-up phone contact will be made with those who have emailed. The recruitment advertisement to be used is provided in online supplemental file 4.

During the phone call, a structured script will be used to conduct a brief screening process. This includes administration of a telephone version of the mRS,^60^ and additional questions aligned with the study’s inclusion criteria. Individuals who appear eligible based on this initial screening will be invited to an in-person eligibility assessment in their respective city. At this appointment, a written informed consent would be sought by the responsible researcher (PP) after which cognitive screening will be conducted using the MoCA, with the resulting score determining final inclusion in the study. The participant information form and informed consent form to be used in the study are provided in onlinesupplemental files 5  6. Figure 1 provides an illustration of the study schematics.

**Figure 1 F1:**
[figure not shown]
Schematics of the study procedure. GOT, Gothenburg; KSD, Karlstad; MMX, Malmö; RGM, Ronnie Gardiner Method; STO, Stockholm.

### Randomisation procedure

Randomisation (1:1) will be conducted in four separate blocks corresponding to each study site: Gothenburg, Karlstad, Stockholm and Malmö. Microsoft Excel will be used for performing the randomisation based on participant identification numbers, with the process managed by an external researcher to ensure objectivity.

### Allocation concealment

An external researcher will be responsible for sending pre-prepared printed letters to both intervention and control groups, which will be placed in sealed envelopes to maintain allocation concealment. Outcome assessors (PP, SG) will remain blinded to group allocation throughout the study period. While complete blinding presents inherent challenges due to the nature of the intervention, several measures will be implemented to minimise assessment bias. Participants will receive explicit instructions not to disclose their group assignment during assessment visits, with these confidentiality instructions included in both written invitation letters and delivered verbally at each assessment session. Assessment protocols will be standardised to minimise opportunities for inadvertent unblinding, and any instances of unblinding will be documented and reported in the final analysis to maintain study integrity.

### Data management plan

Personal data gathered during the study will be pseudonymised immediately on inclusion and handled under strict confidentiality in accordance with Swedish data protection regulations and the University of Gothenburg’s Rules for Research Data Management.^61^ Data containing personal information will be stored on the Nextcloud files platform with regular automated backups and processed within the Trusted Research Environment platform. Paper-based assessment instruments will be archived in the local unit archive under restricted access protocols. All data and study-related documents will be preserved for a minimum 10-year retention period in compliance with institutional guidelines.^61^

Following study completion, anonymised data will be made available through the Swedish National Data Service (SND) repository under restricted access conditions, requiring individual approval for each data request. Interview recordings will not be published due to confidentiality requirements. Given the academic investigator-initiated nature of this study, no external data monitoring committee will be required. A detailed data management plan is provided in online supplemental file 7.

### Sample size calculation

The sample size estimation was conducted using GPower software (V.3.1.9.7). The study’s primary outcome is the between-group difference in change of Mini-BESTest total scores postintervention. Based on Beauchamp *et al*,^62^ a minimal clinically important difference of 4 points was chosen, with a corresponding baseline SD of 6.5 points for the Mini-BESTest in a stroke outpatient cohort. This yields a standardised effect size of Cohen’s d=0.62 with an α error probability of 0.05 and desired power of 80% (1 – β=0.80). GPower indicates that 36 participants per group (72 total) are required to detect the specified effect size. To allow for up to 10% attrition, the total sample size was increased to 80 participants (40 per group).

Given that this is a multicentre trial conducted across four sites, we initially adjusted the sample size as per CONSORT recommendations for non-pharmacological treatments,^63^ to account for potential clustering effects due to differences between sites or instructors. The design effect was calculated by drawing on estimates from multicentre stroke rehabilitation literature, which typically report ICCs ranging from 0.007 to 0.031.^64^ An ICC of 0.01 was conservatively applied, as applying a higher ICC would have led to a larger sample size that was beyond the financial constraints of the current study and would have been unfeasible. Since the intervention will be delivered across four sites, we adjusted for potential clustering using a calculated design effect of 1.17 using the formula [1 + (*n*−1) × ICC], where *n* is the average cluster size and ICC is the intracluster correlation coefficient, which yielded a cluster-adjusted sample size requirement of 84 participants (approximately 21 per site).

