### Quantitative data analysis

All quantitative data will be analysed using both descriptive and inferential statistical methods. Prior to conducting hypothesis testing, data will be assessed for completeness, normality and the presence of outliers. The distribution of continuous variables will be evaluated using visual inspection and the Shapiro-Wilk test to determine the suitability of parametric or non-parametric analyses. Baseline characteristics between the intervention and control groups will be compared using Mann-Whitney U tests for continuous variables and χ^2^ tests for nominal variables to assess group equivalence. All analyses will follow the intention-to-treat principle, meaning that all participants will be analysed in the groups to which they were originally randomised, regardless of adherence or dropout. Any missing data will be managed using appropriate imputation strategies, depending on the pattern and mechanism of missingness. The effects of the intervention on primary and secondary outcomes will be examined using mixed-model repeated measures ANOVA (analysis of variance) or appropriate non-parametric alternatives, with time (baseline, postintervention, 3-month follow-up) and group (RGM vs control) as factors.

To address multiplicity in the analysis of the 13 secondary outcomes (FES-I, Memory Test, Victoria Stroop Test, Rey Complex Figure Test, SPPB, 10MWT, 6MWT, ODTA, 9HPT, SIS-16, MADRS, RAND-36 and EQ-5D-5L), the Benjamini-Hochberg False Discovery Rate (FDR) procedure will be applied to control the expected proportion of false positives. Effect sizes of the variables will be expressed using partial eta squared. All statistical analyses will be conducted using IBM SPSS Statistics (V.29.0.1), with the FDR procedure implemented using the SPSS syntax. A significance level of p<0.05 will be applied for the primary outcome, while FDR-adjusted p values will be used for secondary outcomes.

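### The sample size for a difference in change is standardised by a baseline SD with no correlation stated, and 36 per group does not give 80% two-sided power even on the plan's own d

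*Protocol article*

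**What the plan says.** The Sample size calculation section of the protocol article says that the "primary outcome is the between-group difference in change of Mini-BESTest total scores postintervention". For the inputs it says that "a minimal clinically important difference of 4 points was chosen, with a corresponding baseline SD of 6.5 points for the Mini-BESTest". From these it obtains "d=0.62 with an α error probability of 0.05", aims for 80% power, and reports 36 per group (72 in total). It then gives 80 after a 10% attrition allowance and, after a design effect of 1.17 based on an ICC of 0.01, a final 84.

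The section states no SD of change, no correlation between the baseline and week-12 scores, no test and no sidedness. The Quantitative data analysis section plans a mixed-model repeated measures ANOVA with group and time (three visits) as factors, and says "A significance level of p<0.05 will be applied for the primary outcome".

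**The concern.** A baseline SD measures how much people differ from one another at one visit. A difference in change is judged against how much people differ in their change, and that depends on how strongly the two visits are correlated. The plan names the outcome as a change and the SD as a baseline SD, and nothing connects the two. The stated d is therefore not derived for the stated outcome.

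The 80% power figure is what a funder, ethics committee or later reader will use to interpret a null result. If it does not follow from the inputs, that interpretation has no footing. The plan also says that cost ruled out a higher ICC, so precision available from data already being collected matters here.

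**Working it through.** **Inputs from the Sample size calculation section:** difference 4 points; baseline SD 6.5; alpha 0.05; power 80%; 36 per group; attrition 10%; ICC 0.01; 84 enrolled. The 1:1 allocation is from Study design.

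**Assumptions of this check:** two-sided test; equal SDs at baseline and week 12; r from 0.4 to 0.8, since the document gives none.

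**1. The plan's own figures.** The effect size is 4/6.5 = 0.615, which agrees with 0.62. For the sample size, the normal approximation is n per group = 2(1.960 + 0.842)²/d². This is 15.70/0.379 = 41.5, so 42, for d = 0.615, and 15.70/0.384 = 40.8, so 41, for d = 0.62. The exact two-sample t test (noncentral t) gives 43 and 42. At 36 per group, two-sided power is 73.1% (d = 0.615) or 73.7% (d = 0.62). A one-sided t test needs 33 to 34 per group and has 83% power at 36. Neither version of the t test returns 36. The later steps do follow: 72/0.9 = 80 and 72 × 1.17 = 84.2.

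**2. SD of change.** SD of change = 6.5 × √(2(1 − r)). It equals 6.5 only when 2(1 − r) = 1, that is, r = 0.5. For 36 per group to give 80% two-sided power, it would have to be about 5.97, that is, r of about 0.58.

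| r (assumed) | SD of change | d | n per group for 80% | Power at 36 per group |
|---|---|---|---|---|
| 0.4 | 7.12 | 0.56 | 51 | 65% |
| 0.5 | 6.50 | 0.615 | 43 | 73% |
| 0.6 | 5.81 | 0.69 | 35 | 82% |
| 0.7 | 5.03 | 0.79 | 26 | 91% |
| 0.8 | 4.11 | 0.97 | 18 | 98% |

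**3. Power of the trial as planned.** The final 84 is 72 × 1.17, so attrition still has to come off it: 84 × 0.9 = 75.6 analysed, or 37.8 per group and 18.9 per site. The design effect is 1 + (18.9 − 1) × 0.01 = 1.179. The effective size is 75.6/1.179/2 = 32.06 per group.

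**4. Baseline-adjusted analysis, for comparison.** The residual SD is 6.5 × √(1 − r²).

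| r (assumed) | Change, with design effect | Change, without | Adjusted SD | Baseline-adjusted, with design effect |
|---|---|---|---|---|
| 0.4 | 60% | 67% | 5.96 | 75.4% |
| 0.5 | 68% | 75% | 5.63 | 80.0% |
| 0.6 | 77% | 84% | 5.20 | 85.8% |
| 0.7 | 88% | 93% | 4.64 | 92.5% |
| 0.8 | 97% | 99% | 3.90 | 98.1% |

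Without the design effect, the baseline-adjusted analysis has 82% power at r = 0.4 and 86% at r = 0.5.

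**The case against.** The strongest reply is that no harm has been shown. A cross-sectional SD is a common stand-in when no SD of change is available. The division 4/6.5 is correct. For any r above 0.5 the stand-in errs on the safe side, and the full protocol behind the article may give more. This stands as far as it goes: a reader might infer that using the baseline SD makes the trial underpowered, and the document does not support that, because it gives no r. It does not answer the separate failure in step 1, which involves no r: under a two-sided t test, 36 per group does not follow from the stated d, alpha and power.

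A reader might also infer that 80% is correct for a comparison of raw week-12 scores and has merely been attached to the wrong outcome. It is not: that comparison, with SD 6.5, has the same 73 to 74% power at 36 per group.

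Two further points stand. The baseline-adjusted powers belong to an analysis the plan does not contain, so they show what a change would gain and do not describe the trial as written. And participants are randomised individually within each site, so additive site differences largely cancel between arms and dividing by the full design effect may be too severe. The change-score figures are therefore shown both ways.

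Unstated choices can come near 72 in total. A one-sided Wilcoxon-Mann-Whitney test gives 35 per group. A between-group repeated-measures test on two visits with an assumed r of about 0.7 gives 72. The article states neither, and the second tests an average over visits, not a change.

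**Conclusion.** The point holds in two parts. First, d = 0.62 is the effect size of the stated change outcome only if r is 0.5, and r is not given. The size of this gap is large (51 down to 18 per group for r from 0.4 to 0.8), but its direction is unknown. Second, the stated 80% is not met on the plan's own inputs: 42 to 43 per group are needed, and 36 give 73 to 74%. At r = 0.5, where the baseline SD happens to be right, power for change with 84 enrolled is 68% (75% without the design effect).

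The first part rests on equal SDs at the two visits. The second rests on a two-sided test, which the plan does not state for the calculation. It would be too strong to say that rewording alone recovers 80%: with the design effect, change-score power is still 77% at r = 0.6. Reaching 80% at r = 0.5 requires a different primary analysis.

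**What to change.** In Quantitative data analysis, make the primary analysis the between-group difference in Mini-BESTest at week 12, adjusted for baseline Mini-BESTest. In Sample size calculation, replace 4/6.5 with the effect size for that analysis, using SD 6.5 × √(1 − r²) and noting the equal-SD assumption. State r with its source, state the sidedness, and give the power of 84 enrolled over a range such as r = 0.4 to 0.8 (the last column of the second table, if the design effect is kept).

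If the change-score or repeated-measures analysis is retained, keep the change outcome but restate its power with the SD of change, and drop the 80% claim unless the stated r supports it.

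The cost is one changed primary-analysis sentence, a rewritten sample-size paragraph and possibly a less favourable stated power. No extra participants or visits are needed, since the baseline score is already in the assessment schedule (Table 1).

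### The base sample size of 36 per group does not follow from the stated inputs: d=0.62, α 0.05 and 80% power need 42 per group two-sided, and 36 per group gives about 74% power

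*Protocol article*

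**What the plan says.** All the inputs are in the protocol article, Sample size calculation:

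- Endpoint: "The study’s primary outcome is the between-group difference in change of Mini-BESTest total scores postintervention".
- Difference to detect: "a minimal clinically important difference of 4 points was chosen".
- Variability: "with a corresponding baseline SD of 6.5 points for the Mini-BESTest in a stroke outpatient cohort".
- Effect size, α and power: "standardised effect size of Cohen’s d=0.62 with an α error probability of 0.05 and desired power of 80" per cent.
- Result: "GPower indicates that 36 participants per group (72 total) are required to detect the specified effect size".

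The section then raises the total to 80 for 10% attrition, and gives 84 as the requirement after a design effect of 1.17. It does not state whether the test is one- or two-sided, which GPower test was used, or any correlation between baseline and follow-up.

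Under Quantitative data analysis, outcomes "will be examined using mixed-model repeated measures ANOVA (analysis of variance) or appropriate non-parametric alternatives", and "A significance level of p<0.05 will be applied for the primary outcome".

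**The concern.** The paragraph gives everything needed to repeat a two-group comparison of means, yet 36 per group is too small for d=0.62 at 80% power with a two-sided test and too large with a one-sided test. The figure matters because the rest of the sizing is stacked on it. If the base is too low, the trial has less chance of detecting its own minimal important difference than the 80% it states. A null result could then be read as evidence against the intervention when the trial was less able to detect the effect than advertised.

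**Working it through.** **Inputs.** Difference 4 points, SD 6.5, α 0.05, power 0.80 and attrition 10% (Sample size calculation); 1:1 allocation (Study design). Two-sided testing is assumed, because the planned primary test is a non-directional ANOVA at p<0.05. One-sided is shown as well.

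**Effect size.** d = 4/6.5 = 0.615, rounded in the plan to 0.62.

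**Normal approximation.** n per group = 2(z₁₋α/₂ + z₁₋β)²/d² = 2(1.960 + 0.842)²/0.62² = 40.8, so 41. One-sided: 2(1.645 + 0.842)²/0.62² = 32.2, so 33.

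**Exact calculation.** Two-sample t-test, noncentral t with 2n−2 degrees of freedom and noncentrality d√(n/2). This is the method GPower uses for two independent means.

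| Test | n per group, d=0.62 | n per group, d=0.615 | Power at 36 per group, d=0.62 | Power at 36 per group, d=0.615 |
|---|---|---|---|---|
| Two-sided t | 42 | 43 | 73.7% | 73.1% |
| One-sided t | 33 | 34 | 83.1% | 82.7% |
| Two-sided Wilcoxon–Mann–Whitney, normal data | 44 | 45 | – | – |
| One-sided Wilcoxon–Mann–Whitney, normal data | 35 | 35 | – | – |

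None of these returns 36. Two-sided power at 42 per group is 80.2% (d=0.62).

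**What 36 per group would imply.** A two-sided t-test reaches 80% power with 36 per group at d = 0.670. That is 0.670 × 6.5 = 4.35 points, or equivalently an SD of 4/0.670 = 5.97 with the 4-point difference kept.

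**How the error carries forward.** The plan's later totals do follow from 72:

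- 72/0.9 = 80.
- 72 × 1.17 = 84.2, reported as 84. The multiplication starts from 72, not from the attrition-inflated 80 (80 × 1.17 = 93.6), so the attrition allowance is not in the final number.

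From the corrected base of 2 × 42 = 84:

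- attrition alone: 84/0.9 = 93.3, so 94;
- design effect alone: 84 × 1.17 = 98.3, so 99;
- both: 84 × 1.17/0.9 = 109.2, so 110.

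**Power of the 84 actually planned (two-sided, d=0.62).**

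- No loss, 42 per group: 80.2%.
- 10% loss, 84 × 0.9/2 = 37.8, about 38 per group: 76.0%.
- 10% loss and the plan's design effect, 37.8/1.17 = 32.3 effective per group: 68.9%.

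**Dependence on the unstated correlation r between baseline and week 12.** The values of r are assumptions. The SD of a change score is 6.5√(2(1−r)), and the residual SD under ANCOVA is 6.5√(1−r²), taking the same SD at both times.

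| Assumed r | Change score: n per group | Change score: power at 38 per group | ANCOVA: n per group | ANCOVA: power at 38 per group |
|---|---|---|---|---|
| 0.4 | 51 | 68% | 36 | 83% |
| 0.5 | 43 | 76% | 33 | 87% |
| 0.6 | 35 | 85% | 28 | 92% |
| 0.7 | 26 | 93% | 23 | 96% |

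The n columns use unrounded d = 4/6.5. The power columns use d=0.62; unrounded, ANCOVA at r=0.5 gives 86%.

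**The case against.** Four points can be made for the plan.

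1. *Sidedness is not stated.* With a one-sided test, 36 per group gives about 83% power and exceeds the requirement. This stands as a caveat on the 74%, but it does not rescue the figure: the one-sided t-test answer is 33 or 34, and one-sided sizing does not match the non-directional ANOVA described in the analysis section.
2. *The endpoint is a change score, but the SD is a baseline SD.* True power therefore depends on r. The figures on the stated d describe a change score only at r=0.5, where the change SD equals 6.5. Power is better above that and worse below. This stands: what is shown is that the stated derivation fails, not that the trial must be underpowered.
3. *36 can be reached with other inputs*, for example ANCOVA at r of about 0.4, or a repeated-measures between-group test with f=0.31, two measurements and r=0.7 (total 72). None of these inputs is in the document, and the last tests the time-averaged group effect rather than the difference in change. If such a calculation was run, the paragraph misdescribes it and still needs correcting.
4. *The design effect of 1.17 may be too harsh.* Participants are individually randomised within site, so site differences fall in both arms, and clustering by training group affects only the RGM arm. This stands in part: the 69% is a check on the plan's own terms and probably pessimistic, so the 76% is the safer figure to quote.

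**Conclusion.** The stated 36 per group is wrong for the stated inputs. For a two-sided two-sample t-test at d=0.62, α 0.05 and 80% power, the requirement is 42 per group (43 with d unrounded), and 36 per group gives 73.7% (73.1%). One-sided testing does not give 36 either. The planned 84 matches the uninflated requirement at the rounded d and falls two short of the 86 needed at the unrounded d. On the stated d it gives about 76% power after 10% attrition. These power figures rest on two-sided testing and on 6.5 being the SD of the quantity compared. The plan gives no correlation that would support a more favourable figure.

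**What to change.** In the sample-size paragraph, replace the base of 36 per group (72 total) with 42 per group (84 total) before any inflation, and state that the test is two-sided. Keep 84 as the number that can be recruited, and say plainly that it gives about 76% power for a 4-point difference after 10% attrition and before any clustering allowance. Remove the claim that 84 already includes the attrition and clustering adjustments. If 36 came from a different GPower procedure, report that procedure and all its inputs instead.

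As an option, if the primary analysis is changed to a baseline-adjusted ANCOVA at week 12, restate power on that basis with an explicitly assumed correlation. With 38 per group, power is about 87% at r=0.5 (86% with d unrounded) and 96% at r=0.7. At those correlations the lost power is recovered at the planned enrolment.

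The cost is rewording this paragraph and any matching registry text, and, unless the ANCOVA option is taken, a less favourable stated power. No additional participants are needed.

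### The design effect of 1.17 fits 18 participants per site, but the same sentence gives about 21, for which the plan's own formula yields 1.20 (1.18 after the planned attrition)

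*Protocol article*

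**What the plan says.** All the figures are in the protocol article under Sample size calculation.

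- Unadjusted size: "GPower indicates that 36 participants per group (72 total) are required to detect the specified effect size".
- Attrition: "To allow for up to 10% attrition, the total sample size was increased to 80 participants (40 per group").
- Clustering: "An ICC of 0.01 was conservatively applied". The design effect is 1 + (n − 1) × ICC, n is defined as the average cluster size, and there are four sites. The adjustment is made "using a calculated design effect of 1.17 using the formula".
- Result: a "cluster-adjusted sample size requirement of 84 participants (approximately 21 per site").

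The section does not say which n went into the formula, nor whether 72 or 80 was multiplied by the design effect.

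**The concern.** The formula has two inputs, n and the ICC. The ICC is given, n is defined, and the resulting site size appears in the same sentence as the design effect, so the result can be checked directly. It does not agree: 1.17 belongs to a smaller site than the one the trial will have.

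The slip is easy to make when the number of sites is fixed. Enlarging the total also enlarges each site, so a design effect computed at the size before inflation is too small for the size after it. The error is therefore in the optimistic direction. At stake is the published justification of the sample size: a reader would take 84 as a number that already allows for clustering, when on the plan's formula it falls short of doing so, and falls further short once the planned attrition is counted.

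**Working it through.** **Inputs (Sample size calculation).** Required before adjustment: 72. Attrition: 10%. ICC: 0.01. Sites: 4. Stated design effect (DE): 1.17. Stated total: 84, about 21 per site. Effect size: d = 0.62. α = 0.05, with sidedness not stated.

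**1. Reproduce the plan's figures.**
- The n that gives 1.17: (1.17 − 1)/0.01 + 1 = 18 = 72/4.
- 72 × 1.17 = 84.24, stated as 84.
- Starting from 80 instead: 80 × 1.17 = 93.6, which does not give 84.

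So 84 is reproduced by 72 × 1.17 with 18 per site, and the step to 80 for attrition is not carried into it.

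**2. Apply the formula at the sizes the plan implies.**
- Enrolled, 84/4 = 21: DE = 1 + 20 × 0.01 = 1.20.
- Analysed after 10% attrition, 84 × 0.9 = 75.6 and 75.6/4 = 18.9: DE = 1 + 17.9 × 0.01 = 1.179.

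**3. Effective sample from 84 enrolled.**

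| Case | Analysed | DE | Effective total |
|---|---|---|---|
| No attrition, plan's DE | 84 | 1.17 | 71.8 |
| No attrition, DE at 21 | 84 | 1.20 | 70.0 |
| 10% attrition, plan's DE | 75.6 | 1.17 | 64.6 |
| 10% attrition, DE at 18.9 | 75.6 | 1.179 | 64.1 |

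The cluster-size slip accounts for 71.8 − 70.0 = 1.8 participants without attrition, and 64.6 − 64.1 = 0.5 with it. The rest of the drop from about 72 to about 64 is attrition.

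**4. Power.** Assumption: two-sample t test at d = 0.62, α = 0.05. Because sidedness is not stated, both versions are shown.

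| Effective per arm | Two-sided | One-sided |
|---|---|---|
| 36 (the plan's 72) | 0.737 | 0.831 |
| 35 (70/2) | 0.725 | 0.822 |
| about 32 (64.1/2) | 0.686 | about 0.79 |

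Moving from 36 to 35 per arm costs about 1 percentage point on either version. Moving to about 32 costs about 4 to 5 points.

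**5. Size of the slip in enrolment terms, attrition ignored.** One step: 72 × 1.20 = 86.4. Solved so that the site size matches the total, N = 72 × [1 + (N/4 − 1) × 0.01] gives N = 71.28/0.82 = 86.9. Both compare with 84.

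**The case against.** Four points can be made for the plan.

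**The plan does not promise 72 effective participants.** A reader might infer from the cluster-adjusted requirement of 84 that the authors claim it is worth 72 independent participants. The text does not say so; it gives 72 as the requirement before adjustment. This stands. The comparison with 72 is a comparison with the plan's stated requirement, not a refutation of a stated effective size.

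**1.20 is not the only defensible value.** The plan does not say whether the average cluster size means enrolled or analysed participants, and clustering acts on those analysed. At 18.9 per site the formula gives 1.18, only 0.01 from the stated value. This also stands, and it narrows the slip. It does not rescue the 84, because that reading also reduces the analysed total to 75.6.

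**The consequence is marginal.** The gap between 84 and 86.4 or 86.9 is 2 to 3 participants, and it changes no decision. This is correct for the slip taken alone. A reader might conclude that the trial must enrol 87, or 88 for equal arms. The documents do not support that as the requirement, because those numbers leave out the plan's own 10% attrition.

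**The formula fits this design poorly.** Under Randomisation procedure, individuals are randomised 1:1 within each site, whereas the formula with n equal to a whole site describes allocation of whole clusters. This is a fair reservation about treating 1.20 as the true variance inflation. The present point is narrower: the plan's formula, definition and site size do not agree with the design effect it reports.

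**Conclusion.** The point holds as a minor internal inconsistency. The stated 1.17 corresponds to 18 per site, while the same sentence gives about 21, where the formula yields 1.20, or 1.18 at the analysed 18.9. On the plan's own formula, 84 enrolled are worth about 70 independent participants with complete data and about 64 after 10% attrition, against 72 required.

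The cluster-size slip by itself costs about 2 effective participants and about 1 percentage point of power. It does not show that the trial is materially undersized. The larger part of the shortfall arises because the attrition allowance is not carried into the 84.

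These figures assume the plan's ICC of 0.01, four equal sites, the 10% attrition spread evenly, and the plan's formula taken as given. The power figures also assume a t test at d = 0.62. The two-sided value at 36 per arm is 0.737, not the 80% stated, so they should be read as differences between scenarios and not as support for the base figure of 72.

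**What to change.** No extra enrolment is needed for this point. Where the formula is kept, amend the last sentence of Sample size calculation as follows:

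- State the cluster size used, and whether it is enrolled or analysed.
- Give the design effect at that size: 1.20 at 21 enrolled per site, 1.18 at 18.9 analysed per site.
- Replace the description of 84 as the cluster-adjusted requirement with the effective sample that 84 delivers: about 70 without attrition and about 64 with the planned 10%.
- Report the power at those two sizes, with the sidedness stated. At d = 0.62 this is 0.725 and 0.686 two-sided, or 0.822 and about 0.79 one-sided.
- Do not put 87 or 88 in place of 84 as the requirement, since neither includes attrition.

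The cost is one or two rewritten sentences and a less favourable stated effective sample and power.

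### The recruited 84 is 72 × 1.17, so it carries the clustering factor but not the 10% attrition allowance; by the plan's own formula both together need 94

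*Protocol article*

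**What the plan says.** All the steps are in the protocol article, under Sample size calculation.

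- Target difference: "a minimal clinically important difference of 4 points was chosen".
- Standard deviation and effect size: the spread is taken from the same source, "with a corresponding baseline SD of 6.5 points for the Mini-BESTest in a stroke outpatient cohort". The resulting inputs are then given: "This yields a standardised effect size of Cohen’s d=0.62 with an α error probability of 0.05 and desired power of 80"%.
- Base: "GPower indicates that 36 participants per group (72 total) are required to detect the specified effect size".
- Attrition: "To allow for up to 10% attrition, the total sample size was increased to 80 participants (40 per group").
- Clustering, in the next paragraph: "An ICC of 0.01 was conservatively applied", and the adjustment was made "using a calculated design effect of 1.17", from the formula 1 + (n − 1) × ICC with n the average cluster size, "which yielded a cluster-adjusted sample size requirement of 84 participants (approximately 21 per site").

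The abstract gives 84 (42 per arm) as the number to be recruited, so nothing is added after the clustering step. The section does not say which number the design effect multiplies, and it does not say that the attrition allowance was withdrawn.

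**The concern.** The section makes two adjustments in turn, attrition and then clustering, and ends on a number larger than 80. A reader will take 84 to cover both. But 84 is only 5% more than 80 (84/80 = 1.05), whereas the stated clustering factor is 17%. The two cannot both be contained in 84 if 72 is the starting point.

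This is the sample size for the primary outcome. If the attrition allowance is not in it, a trial that loses the proportion it planned for falls below its own requirement, and the power quoted in the section does not describe the trial being recruited.

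**Working it through.** **Inputs (protocol article, Sample size calculation and abstract).** Required evaluable N = 72 (36 per arm); attrition up to 10%; ICC 0.01; four sites; design effect 1.17; d = 0.62; α = 0.05 with sidedness not stated; final N = 84.

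**Step 1. Reproduce the attrition step.** 72/0.9 = 80. This matches.

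**Step 2. Find the base of the design effect.** DE = 1 + (n − 1) × 0.01.

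| Total N | n per site | DE |
|---|---|---|
| 72 | 18 | 1.17 |
| 80 | 20 | 1.19 |
| 84 | 21 | 1.20 |

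Only the pre-attrition 72 gives the stated 1.17.

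**Step 3. Reproduce the final figure.** 72 × 1.17 = 84.24, the stated 84 to within rounding. From the attrition-inflated base, 80 × 1.17 = 93.6, or 80 × 1.19 = 95.2; neither is 84.

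**Step 4. Apply both allowances.** 72 × 1.17/0.9 = 93.6, so 94 (47 per arm). The order does not matter, since 80 × 1.17 is also 93.6. With the design effect at 20 or 21 per site the total is about 96. Over the ICC range that the section cites, at 18 per site: ICC 0.007 gives 72 × 1.119/0.9 = 89.5, so 90; ICC 0.031 gives 72 × 1.527/0.9 = 122.2, so 123 (124 for equal arms).

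**Step 5. What 84 delivers by the plan's own method.** With the full 10% loss, 84 × 0.9 = 75.6 completers. Divided by 1.17 this is 64.6 effective participants, or 32.3 per arm, against the required 72. The ratio is 64.6/72 = 0.90.

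**Step 6. Power (two-sample t test, noncentral t, d = 0.62, α = 0.05).**

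| Effective n per arm | Two-sided | One-sided |
|---|---|---|
| 36 (the plan's requirement) | 73.7% | 83.1% |
| 32.3 (84 randomised, 10% lost, DE 1.17) | 68.9% | 79.4% |

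The change down each column is what the missing attrition allowance costs: 4.8 points two-sided, 3.7 points one-sided.

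**Step 7. Sensitivity to the form of clustering.** Randomisation is 1:1 within each site (Randomisation procedure). Suppose instead that clustering arises only among those trained together, with one RGM group per site (an assumption). After 10% loss there are 37.8 per arm, so 37.8/4 = 9.45 per group. The RGM-arm factor is 1 + 8.45 × 0.01 = 1.0845, the average over the two arms is (1 + 1.0845)/2 = 1.042, and the effective N is 75.6/1.042 = 72.5. The same calculation gives 73.4 at ICC 0.007 and 66.8 at ICC 0.031.

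**The case against.** Four points on the other side deserve weight.

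*The article never says that 84 includes attrition.* It attaches the allowance to 80 and calls 84 only cluster-adjusted. That is true, and the fault is one of implication. But 84 is the recruitment target with nothing added afterwards, and the allowance is not withdrawn anywhere, so the text still needs correcting. Ten per cent is also the upper limit of the planned loss, so 75.6 completers is the plan's worst case.

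*The power loss can be overstated.* A reader might set 68.9% against the stated 80% and charge the whole gap to the lost allowance. The figures do not support that. Two-sided, 36 per arm gives only 73.7%; the gap from there to 80% arises because 72 does not reproduce from d = 0.62 (42 per arm are needed two-sided, 33 one-sided). That is a separate problem, and rebuilding the total from another base belongs with it. One-sided, 79.4% is close to the stated 80%.

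*The shortfall depends on a design effect that may not fit.* A reader might infer that the trial really is 10% short of information. The documents do not establish this. With individuals randomised within site, differences between sites fall on both arms, and Step 7 shows that clustering in the RGM arm alone leaves about 72.5 at ICC 0.01. This objection stands against the size of the shortfall. It does not repair the published derivation, which chose 1.17 and applied it to the whole sample.

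*Imputation under intention to treat keeps every participant in the analysis.* It does not restore the information lost with dropouts, and the plan itself chose to inflate for attrition.

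The section cites financial limits, but as the reason for not using a higher ICC, not for omitting attrition.

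**Conclusion.** The point holds as a fault in the derivation. The stated design effect and the stated total both come from the pre-attrition 72, so 84 covers clustering by the plan's formula and makes no provision for dropout. Both allowances need 94, about 10 more than the trial will recruit.

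The attributable loss is 4 to 5 percentage points of power, depending on sidedness. It assumes the plan's 72, its design effect of 1.17 on both arms, d = 0.62 and the full 10% attrition. Under clustering in the RGM arm only, the effective sample is near the required 72 at the plan's ICC and below it at the top of the cited ICC range.

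**What to change.** Choose one of two courses in the sample size section.

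1. Keep 84 and say what it is: 72 multiplied by 1.17, with no attrition allowance. Report the power at 84 randomised with 10% attrition under the stated design effect, and name the sidedness: 68.9% two-sided or 79.4% one-sided at d = 0.62.
2. Recompute once from the planned analysis, with a clustering factor that fits randomisation within site and the attrition allowance included, and report the power that 84 then gives.

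Either way, remove the impression that 84 allows for 10% attrition. Reporting the power at 84 changes wording only: recruitment, allocation, outcomes and analysis stay as they are. Under the first course the cost is a less favourable power statement; under the second the figure depends on the clustering factor that can be justified.
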